#### Intervention

Intervention for patients in the intervention group (in addition to usual care) will include an Android-based application that has all the functional requirements approved by the experts in the analysis and software design phases. This application will contain audio, video, textual files and games to improve lower and upper limb function and activities of daily living, prevent and reduce depression, reduce and manage pain and other possible complications of stroke, medication reminders and whatever playing a role in improving patient outcomes, and will be designed according to experts' opinion. Patients will be advised to use the application 5 days a week and for a period of 1 h each day. The duration of the intervention will be 8 weeks (40 sessions in total). A systematic review study [21] showed that the duration of intervention to improve physical activities using mobile phones was between 4 and 6 weeks, which could be extended to 10 weeks for greater effectiveness. According to the conditions in the country and the opinion of experts and follow-up protocols of patients, intervention for more than 8 weeks was not recommended due to the possibility of excessive sample fall. Patients will access the application by creating valid accounts. Account creation by patients and physicians will be done by the system admin and demographic information will be recorded for them; however, the usernames defined for users cannot be changed by them. The application can record the number of times and hours of application use by the user. In order to learn how to use the application, users can contact one of the research team members. A member of the research team will also make weekly phone calls to make sure patients know how to use the application. Intervention for patients in the control group will include usual medical care based on the opinion of the responsible neurologist (This can include physiotherapy or occupational therapy). An application will be installed on the smartphones of these individuals which lacks the main capabilities of the application and only contains electronic questionnaires. Installation of this application will be done only for blinding purposes. Intervention duration and the time of measuring the outcomes will be the same for both groups. Figure 2 shows the flowchart of protocol for interventional trial. Re-stroke will be recorded in both groups and finally it will be considered as one of the complications of stroke in both groups. Nevertheless, an individual with re-stroke during the intervention due to entering the acute phase of the disease will be excluded from the study and replaced by another individual. To replace the new individual, the researcher will return to the hospital and replace another person who meets the study inclusion criteria (In case of excessive sample fall). The research hypothesis is that using the proposed intervention along with usual care can improve stroke outcomes. Therefore, this study can be considered as a superiority trial. Routine rehabilitation interventions (such as electrotherapy) cannot be eliminated at this time. Therefore, no hypothesis can be defined for this intervention alone.

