#### Randomization

Randomization will be done by block method (Permuted Block Randomization) in a way that first all foursome blocks which include two codes A and B will be prepared (6 blocks) and then, using a table with random numbers, random blocks will be selected by placement (15 blocks). These blocks will contain up to 60 codes including A and B, each of which will be randomly assigned to either the control or the intervention group. This table will be generated by MS Excel 2019 and function of RANDBETWEEN (1,6).

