#### Data collection

The required data will be collected using valid and reliable questionnaires that are introduced as follows. Data will be collected in three stages: prior to intervention (before the intervention and at the time of discharge), two months after the intervention and three months after the intervention (in the doctor's office or in the hospital outpatient clinic). Data from National Institute of Health Stroke Scale (NIHSS) and Barthel Index (BI) questionnaires and stroke complication checklist will be filled out by the attending neurologist and other questionnaires will be filled out by patients as self-report. Completion of questionnaires by patients will be done electronically and sent online through the application. Therefore, this survey will be considered as a “closed survey” since only registered users with a valid account can access the questionnaires and submit them. Application features will be inactive until patients, complete questionnaire items. After completion, application features will be activated and the questionnaire will be deactivated to prevent response duplications. The questionnaires will be reactivated two months and three months later. In order to ensure that no data will be missing, all fields and questions will be defined as mandatory in electronic questionnaires and patients will be warned to answer all questions before sending the questionnaire.

All online questionnaires will exactly be designed the same as paper questionnaires in terms of appearance, content and sequence of questions. That is, all the questions will be placed consecutively and not on separate pages. Therefore, it can be said that the validity and reliability reported for the paper version of questionnaire will also apply to the electronic version.

It is expected that the use of this application can improve the measured variables in the intervention group compared to the control group. Specifically, the research hypotheses are that patients in the intervention group have significant differences with those in the control group in terms of indicators of physical activity, depression, quality of life, medication adherence, satisfaction with treatment, and the number of complications.

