#### Data analysis

Data analysis will be performed using IBM SPSS 22 [43]. The data will be entered anonymously using codes and numbers, which can be decoded only by one of the researchers (except the assessor or the analyst). The data will be stored in this software application and supported by a backup on another system kept in another place. The data will be first presented in the form of descriptive statistics and frequency distribution tables. The normality of the data will be checked using the Kolmogorov–Smirnov test. Depending on the type of data distribution, the mean or median of the data will be used as a criterion. In case of normal distribution of data, the mean will be used and in case of abnormal distribution (non-parametric), the median will be used for statistical calculations. In order to determine the relationship between the scores of patients’ activities of daily living, quality of life, depression, medication adherence and patient satisfaction with patients’ group type (control or intervention), an independent t-test will be used. If there is a significant difference between the intervention group and the control group, the effect of the intervention will be specified. Repeated measures analysis of variance (ANOVA) will also be used to analyze multivariate and control the effects of confounding variables on dependent variables. Confounding variables will include: patient age, sex and educational level, which can affect the final results. In all tests, a significance level of 0.05 will be considered. Pearson or Spearman correlation coefficient (according to the type of variable distribution) will be used to determine the relationship between the usage duration of the program and the score of the measured variables. After categorizing the time of application usage, one-way ANOVA or Kruskal–Wallis’s test (depending on the type of variable distribution) will be used to determine the relationship between the measured variables and the time of application usage. Chi-square test will be used to determine the relationship between the type of complications in both groups. Also, to determine the relationship between the scores of the measured variables before and after the intervention, a paired t-test will be used in each group separately. Hypothesis H0 will indicate the absence of correlation and Hypothesis H1 will indicate the existence of correlation between the measured variables.

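### Randomised patients who have a re-stroke during the intervention are excluded from the study, which can bias the group comparison in either direction

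*Protocol article*

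**What the plan says.** The rule is in the Intervention section of the protocol article. It first makes re-stroke an outcome: "Re-stroke will be recorded in both groups and finally it will be considered as one of the complications of stroke in both groups". The next sentence says that a patient with a re-stroke while the intervention is running, "due to entering the acute phase of the disease will be excluded from the study and replaced by another individual". On replacement, "the researcher will return to the hospital and replace another person who meets the study inclusion criteria (In case of excessive sample fall"). That closing qualifier is attached to the replacement and not to the exclusion, and no threshold for excessive loss is given.

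Three other sections bear on this:

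- Data collection schedules follow-up at two and three months. It lists among the between-group hypotheses "satisfaction with treatment, and the number of complications".
- Data analysis states: "Chi-square test will be used to determine the relationship between the type of complications in both groups". It names no denominator.
- Randomization describes 15 blocks of four: "These blocks will contain up to 60 codes including A and B". Study design and setting plans 66 patients, 33 per group, after a 10% dropout allowance.

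**The concern.** Randomisation makes the two groups comparable as allocated. The rule removes patients according to something that happens afterwards. That event is one of the trial's own outcomes, and the application is meant to reduce complications of stroke and includes medication reminders, so its frequency may differ by arm. Patients with a second stroke are likely to have poor scores on NIHSS, Barthel, depression and quality of life. If they leave one arm more often than the other, the remaining groups are no longer the randomised ones.

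The direction is not fixed. More re-strokes among controls would remove poor control outcomes and understate a benefit. More in the intervention arm would hide a harm. The Discussion itself acknowledges possible harm during exercise.

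The wording is exclusion from the study, not merely from use of the application. Read plainly, the later assessments are not made, and no analysis plan can recover data that were never collected.

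**Working it through.** **1. The plan's own sample-size figure.** Inputs from Study design and setting: z-values 1.96 and 1.282, SD 8 in each group, NIHSS means 5 and 12.

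n = (1.96 + 1.282)² × (8² + 8²) / (5 − 12)² = 10.51 × 128 / 49 = 27.46 per group.

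The plan states 27, raised to 30, then 30 × 1.10 = 33. The figure is reproduced, apart from rounding down instead of up to 28.

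**2. Is replacement needed for power?** On the same inputs (difference 7, SD 8, two-sided 0.05):

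| Analysed per group | Power |
|---|---|
| 33 | 94.5% |
| 32 | 93.8% |
| 31 | 93.1% |
| 30 | 92.3% |
| 28 | 90.6% |

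Losing three per group, or even five, leaves power above the planned 90%.

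**3. How often would the rule be used?** The documents give no re-stroke rate. For an assumed 8-week rate p among 66 patients, the expected number is 66p and the chance of at least one is 1 − (1 − p)^66:

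| Assumed p | Expected exclusions | Chance of at least one |
|---|---|---|
| 1% | 0.7 | 48% |
| 3% | 2.0 | 87% |
| 5% | 3.3 | 97% |
| 10% | 6.6 | 99.9% |

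**4. Possible shift in the NIHSS difference.** Let the re-stroke rates be p_C (control) and p_I (intervention), and let a re-stroke add D points to the follow-up NIHSS in either arm. Over all randomised patients, the control-minus-intervention difference is d + (p_C − p_I) × D, where d is the difference among patients without re-stroke. After exclusion only d remains, so the shift is (p_C − p_I) × D. All values of p and D below are assumptions.

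| p_C vs p_I | D = 4 | D = 8 | D = 12 |
|---|---|---|---|
| 5% vs 5% | 0 | 0 | 0 |
| 5% vs 2% | 0.12 | 0.24 | 0.36 |
| 10% vs 5% | 0.20 | 0.40 | 0.60 |
| 10% vs 3% | 0.28 | 0.56 | 0.84 |

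As a share of the planned 7 points, 5% vs 2% gives 0.12/7 to 0.36/7, or about 2% to 5%; 10% vs 3% gives 0.28/7 to 0.84/7, or 4% to 12%. Swapping the arms reverses the sign.

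**5. What is left undefined.** The allocation list holds 15 × 4 = 60 codes against 66 planned patients; 66 / 4 = 16.5, so 17 blocks would be needed. The list therefore has no spare codes for replacements, and the article does not say which code a replacement receives. Nor does it say whether the excluded patient, the replacement or both enter the denominator of the complications comparison.

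**The case against.** The strongest reply has four parts.

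- **Counting the event.** A reader might infer that excluding these patients flatly contradicts counting re-stroke as a complication. The text does not support that. The event can be recorded and tallied before the patient leaves, and nothing says that complications are counted only among those who remain. What is true is narrower: the patient's later scores and later complications are lost, and the denominator is not stated.
- **Allocation of replacements.** A reader might infer that replacements are hand-picked and not randomised, so that a share of an arm is non-randomised. The article says how a replacement is found, not how that person is allocated. The replacement could take the next code or inherit the vacated one. The replacement must meet the same inclusion criteria, and the whole sample is a convenience sample. The shortage of codes leaves the matter unclear, which is not evidence of non-random allocation.
- **The qualifier.** Replacement is tied to excessive loss, so it may seldom be used. This stands for replacement. It does not touch the exclusion, which carries no such limit and is enough to cause the bias.
- **Size.** The exclusion covers only the 8 weeks of intervention, events may be few, and the shift may be small or zero. This stands too. The documents give no rate, so neither a large nor a negligible bias can be claimed from them.

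A practical objection also stands. Some patients will be unable to complete the self-report questionnaires after a re-stroke, so keeping them in the study does not guarantee complete data.

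**Conclusion.** The point holds in limited form. As written, the plan removes randomised patients because of a post-randomisation event that is a counted outcome and that the intervention could affect. This can bias the two- and three-month comparisons in either direction. On NIHSS the shift is zero with equal rates and effects, and about 0.1 to 0.8 points under the assumed scenarios. Those figures rest wholly on assumed rates and an assumed excess score, and they illustrate the mechanism rather than estimate the bias.

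Neither a strict contradiction nor non-random replacement is shown. The allocation of replacements and the complication denominator are simply not stated. Power gives no reason to keep the rule: on the plan's own inputs, the 10% allowance already covers a few losses. The point deserves correction despite its uncertain size, because follow-up that is not collected cannot be restored at analysis.

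**What to change.** In the Intervention section, delete the exclusion and replacement of patients with a re-stroke. State instead that:

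- every randomised patient stays in the assigned group, and the scheduled two- and three-month assessments are attempted after a re-stroke;
- the analysis is by group as randomised;
- re-strokes are counted over all randomised patients, by group;
- results without re-stroke patients are shown only as a sensitivity analysis;
- a rule is set in advance for patients who die or cannot respond.

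Whether use of the application continues after a re-stroke is a separate clinical decision, and this change does not settle it.

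The cost is protocol wording, effort to complete visits already scheduled for a few patients, slightly more variable scores, and some missing self-report data that the pre-set rule must handle. No larger sample is needed.

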
**Fig. 2 Fig2:**
[figure not shown]
Protocol for interventional trial

#### Data collection

The required data will be collected using valid and reliable questionnaires that are introduced as follows. Data will be collected in three stages: prior to intervention (before the intervention and at the time of discharge), two months after the intervention and three months after the intervention (in the doctor's office or in the hospital outpatient clinic). Data from National Institute of Health Stroke Scale (NIHSS) and Barthel Index (BI) questionnaires and stroke complication checklist will be filled out by the attending neurologist and other questionnaires will be filled out by patients as self-report. Completion of questionnaires by patients will be done electronically and sent online through the application. Therefore, this survey will be considered as a “closed survey” since only registered users with a valid account can access the questionnaires and submit them. Application features will be inactive until patients, complete questionnaire items. After completion, application features will be activated and the questionnaire will be deactivated to prevent response duplications. The questionnaires will be reactivated two months and three months later. In order to ensure that no data will be missing, all fields and questions will be defined as mandatory in electronic questionnaires and patients will be warned to answer all questions before sending the questionnaire.

All online questionnaires will exactly be designed the same as paper questionnaires in terms of appearance, content and sequence of questions. That is, all the questions will be placed consecutively and not on separate pages. Therefore, it can be said that the validity and reliability reported for the paper version of questionnaire will also apply to the electronic version.

It is expected that the use of this application can improve the measured variables in the intervention group compared to the control group. Specifically, the research hypotheses are that patients in the intervention group have significant differences with those in the control group in terms of indicators of physical activity, depression, quality of life, medication adherence, satisfaction with treatment, and the number of complications.

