**Discussion:**

The assessed outcomes will include stroke severity using National Institute of Health Stroke Scale (NIHSS) score, ability to perform activities of daily living using Barthel Index (BI) score, depression rate using Beck Depression Inventory (BDI-II) score, quality of life using EQ-5D-3L score, medication adherence using Modified Morisky Medication Adherence Scale (MMAS-8) score, patient satisfaction using Patient Satisfaction Questionnaire (PSQ) score and the number and type of complications in patients in two groups. These outcomes will be assessed at baseline, after two months and after three months from the beginning of the intervention. Intervention effects on the measured variables will also be evaluated using appropriate statistical tests based on the type of variable distribution. Potential consequences of the study might be the improvement of the measured variables in the intervention group compared to that of the control group. The expected results are that the intervention may significantly improve the status of the measured variables in the intervention group compared to that of the control group. If the outcomes of the intervention group do not change significantly compared to those of the control group, it can be due to different reasons. However, this can most likely be attributed to incorrect or insufficient use of the application by patients.

*Trial registration*: This protocol is registered in the Iranian registration of clinical trial (IRCT) on November 7, 2020 with the code IRCT20201015049037N1. URL: https://irct.ir/trial/51674

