#### Blinding

For the purpose of blinding, an application will be installed on the smartphones of patients of both intervention and control groups. The program installed for patients in the control group will only contain online questionnaires that patients need to complete and submit at specified intervals. Online questionnaires will include a number of questions used to measure the target variables. However, the program installed on the phones of participants in the intervention group will include all the capabilities and requirements of the self-care program designed in the design phase. Patients will not be familiar with the nature and content of the installed program on the opposite group’s phones. During program installation, someone other than the assessor physician will install the program for patients or their caregivers. Furthermore, during the assessment process, the same person will record the results of the physician evaluation and the scores related to each patient. Therefore, the assessor physician will not know which group a given patient belongs to. Numeric codes for intervention and control groups will also be used for analysis, and the letters A and B will be used for the control and intervention groups when information is sent to the analyst.

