All instructions and exercises in the application will be approved by the experts to be considered safe for patients to minimize the possibility of causing harm. To eliminate the risk of possible harm to patients during exercise, they will be advised to start the training with an easy level and to make sure that the exercises are done in the presence of a caregiver, and that the way to receive support from a caregiver is fully taught in the application through videos. All of the ethical considerations in clinical trials (including Helsinki ethical codes) will be considered by researchers. If medical complications arise during the study; patients will be treated for free by the responsible physician. Compensation in this regard will be done according to the laws of the Medical System Organization.

For auditing the trial, after registering each sample, a researcher will monitor the patient registration process and assign them to either the control or intervention group using the admin-side application. The completion of questionnaires by patients will also be monitored by this person. If the questionnaires are not filled out, patients will be reminded though a phone call. Filling out the questionnaires will be audited two and three months after patient registration and the necessary actions will be done in case of possible delays. These actions will include sending reminders through the application, sending messages and making phone calls.

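### As written, the four patient-reported baselines are completed inside an arm-specific program, so they are taken after allocation, although before any use of the app features

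*Protocol article*

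**What the plan says.** All references are to the protocol article.

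- **Who completes what (Data collection).** NIHSS and Barthel "questionnaires and stroke complication checklist will be filled out by the attending neurologist and other questionnaires will be filled out by patients as self-report". That leaves EQ-5D-3L, BDI-II, MMAS-8 and PSQ to the patient. The Abstract says of all seven outcomes: "These outcomes will be assessed at baseline, after two months and after three months from the beginning of the intervention".
- **How patients answer (Data collection).** "Completion of questionnaires by patients will be done electronically and sent online through the application". Access is limited to people with an account. The forms are switched on again at two and three months, so their first opening is the baseline.
- **What is installed (Blinding).** "The program installed for patients in the control group will only contain online questionnaires that patients need to complete and submit at specified intervals", whereas "the program installed on the phones of participants in the intervention group will include all the capabilities and requirements of the self-care program".
- **When the arm is set (Discussion, on auditing).** Once a patient is registered, "a researcher will monitor the patient registration process and assign them to either the control or intervention group using the admin-side application".
- **The lock (Data collection).** "Application features will be inactive until patients, complete questionnaire items".
- **Timing.** Data collection puts the first assessment ahead of the intervention, at discharge. No section says that it comes before allocation. The Intervention section states that outcomes are measured at the same times in both arms.
- **Use of baseline (Data analysis).** Scores are compared between arms by independent t-test and before-after within each arm by paired t-test. A repeated measures ANOVA is also planned, with age, sex and education as the named confounders.

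**The concern.** A baseline is a neutral reference only if allocation cannot have influenced it. The usual guarantee is to collect it before the arm is known. Here the patient answers questions on mood, quality of life, adherence and satisfaction inside a program whose build already depends on the arm. Patient blinding rests on not knowing what the other arm received; it does not hide the patient's own program. Knowledge of the arm at baseline is therefore plausible.

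The incentive to submit also differs. In the app arm the self-care features stay closed until the forms are done. In the control arm nothing is withheld, and usual care proceeds regardless. An allocated patient who never submits loses the intervention in one arm and nothing in the other. Delay and non-submission between allocation and baseline could therefore differ by arm.

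At stake is any analysis that reads change from these four baselines.

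**Working it through.** The plan gives no figure on this point. Its one computed figure, the sample size of 27 per group, comes from NIHSS means and does not depend on it. The main check is of the order of steps.

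**1. Count of outcomes.** Seven outcomes have a baseline. Three (NIHSS, Barthel, complications) are recorded by the neurologist. Four (EQ-5D-3L, BDI-II, MMAS-8, PSQ) are self-reported. So 4/7 = 57% of the outcomes are concerned.

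**2. Order of steps.**
- The self-report baseline needs the installed program and an account (Data collection).
- The installed program is one of two builds, chosen by arm (Blinding).
- The arm is set in the admin application at registration (Discussion).
- Hence registration and assignment come first, then installation of the arm's build, then the self-report baseline, then, in the app arm, release of the features.

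A patient cannot answer inside an arm-specific build before the arm is known. This is an inference from three sections; the article does not state the order in one place. The flowchart (Fig. 2) is not shown. If it puts baseline before randomisation, it conflicts with the text and the two need reconciling.

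**3. What the lock does.** It keeps the app-arm baseline ahead of any use of the features, so calling that baseline pre-intervention is accurate. It does not make it pre-allocation. It sets an order, not a deadline, and it can bind only where features exist.

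**4. Which analyses use these baselines.**

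| Planned analysis | Uses baseline? |
|---|---|
| Independent t-test on follow-up scores | No |
| Paired t-test within each arm | Yes |
| Repeated measures ANOVA | Yes, if baseline is one of the time points |
| Adjustment for a baseline score | Not planned |

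**5. Illustration of size (assumptions only).** The documents give neither a baseline shift nor a baseline to follow-up correlation. Assume that allocation shifts one arm's baseline by δ SD, that there is no true effect, that n = 30 per group (the 60 codes under Randomization), and that the correlation is ρ. For a two-sided 5% test of change between arms:

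z = δ / [√(2(1 − ρ)) × √(2/n)]; rejection rate = 1 − Φ(1.96 − z) + Φ(−1.96 − z).

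Example, δ = 0.2 and ρ = 0.5: √(2 × 0.5) = 1; √(2/30) = 0.258; z = 0.2/0.258 = 0.775; rate = 0.118 + 0.003 = 12.1%.

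| δ (SD) | ρ = 0.3 | ρ = 0.5 | ρ = 0.7 |
|---|---|---|---|
| 0.1 | 6.2% | 6.7% | 7.9% |
| 0.2 | 10.0% | 12.1% | 17.0% |
| 0.3 | 16.6% | 21.3% | 32.3% |

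With two time points this test equals the group-by-time test of the repeated measures ANOVA. With the planned three it is one component of that test. The table shows how sensitive a change analysis is; it does not predict a shift in this trial.

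**The case against.** The strongest defence is that the lock protects the baseline. With features closed, the usable part of both programs at that moment is the questionnaires, and patients are not told what the other arm's program holds. BDI-II also asks about the preceding two weeks, so at discharge it largely covers time before allocation. A condensed article may leave step order to the full protocol or to the flowchart. All of this lowers the likely size of the problem. None of it puts baseline before allocation.

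A reader might infer more than the documents support:

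- **That only the app arm has to complete the baseline.** Not so. Control patients are also required to submit, all items are mandatory, and monitoring and reminder calls are not limited to one arm. The asymmetry is only that the app arm has something withheld.
- **That control baselines will come late and flatter the app.** No such delay is described; equal measurement times and a discharge baseline are stated for both arms. The effect of a late baseline is also unsettled. Data collection can be read as timing the later forms from completion, which moves the whole window, while the Discussion audits from registration, which would shorten the interval. Any SD figure for this would be pure assumption.
- **That the bias favours the app.** If learning one's arm lifts mood or satisfaction in the app group, its baseline looks better and its change smaller.
- **That patients are trained before baseline.** Study design mentions training but gives no order relative to the questionnaires.
- **That covariate adjustment is spoiled.** No baseline score is a planned covariate.
- **That all seven baselines are affected.** Nothing shows that the neurologist's ratings follow allocation.

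**Conclusion.** The point holds in a limited form. The text places the EQ-5D-3L, BDI-II, MMAS-8 and PSQ baselines after allocation and before exposure. Knowledge of the arm, or differing delay or non-submission, could affect them, in a direction and by an amount that the documents do not settle. The exposure is confined to the within-group paired t-tests and the repeated measures ANOVA for these four outcomes. A t-test of follow-up scores is untouched; one applied to change scores would not be. The NIHSS-based sample size does not change.

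The conclusion rests on reading Blinding literally, as two builds installed by arm, and on the unseen flowchart not overriding that text. It is more than a request for detail: the described workflow creates a bias risk that a change of order removes, and the analysis cannot reliably undo it afterwards.

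**What to change.** Fix the order in the protocol:

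1. At discharge every patient completes the four self-report instruments on the same questionnaire-only build, which is already planned for the control arm. The paper forms, which Data collection treats as equivalent, would also serve. State that the neurologist's three baseline ratings are likewise complete by then.
2. Only after the baseline is submitted does the admin application release the patient's allocation.
3. The self-care features are then installed or unlocked in the app arm.
4. State that a patient without a submitted baseline is not randomised, and bring the flowchart into line.

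The cost is a small change to the app or admin workflow and a short wait at discharge. No extra visit, staff or patients are needed. If patients have already been enrolled in the other order, report the order actually followed, and for these four outcomes rest the arm comparison on follow-up scores rather than on change.
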